### Secondary outcome measures

Secondary outcomes comprise the following:

#### Physical and psychological symptom subscale of the Ger*man PMS Symptom Diary*
16

To test whether an OLP response occurs primarily on physical or on psychological symptoms, the above-mentioned German PMS Symptom Diary is used including the aforementioned calculation methods. The following scores are derived from the diary data of three menstrual cycles:

Psychological symptom subscore: 14 items of the German PMS symptom diary are considered: depressed mood, hopelessness, feeling of worthlessness, feeling anxious, feeling tensed or being stressed out, irritability, sudden attacks of sadness, sudden crying, sensitivity to rejections, feeling angry, controversies with others, loss of interest in common activities, impaired concentration, feeling out of control or overwhelmed.Physical symptom subscore: The following seven items are considered: breast tenderness, breast sensitivity, breast swelling, headache, joint pains, muscle pain, feeling of a general body swelling, weight gain.

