### Secondary objectives

To test whether an OLP response is observed for somatic or on psychological symptoms.To assess the effect of the OLP treatment on PMS impact.To evaluate the effect of the OLP intervention on quality of life.To assess whether there is any impact of elevated baseline anxiety or depression levels on the OLP response.To investigate whether there is any effect of the OLP intervention on relationship satisfaction.To assess whether positive attitudes towards complementary medicine are associated with OLP responses.To assess the impact of attitudes towards placebos on the OLP response.To evaluate whether the appraisal of the treatment provider has any effect in regard of the OLP effect.To evaluate the intervention credibility in the two intervention groups.To investigate whether expectancy of relief and desire for relief have an effect on the OLP response.To assess treatment adherence of placebo pill intake.

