## Outcome measures: primary, secondary and tertiary

### Primary outcome measures

The German PMS symptom diary consists of 27 symptoms and of three further items assessing interference in different domains (ie, work or school; social activities; relations with others). Usually, a four point Likert scale is employed, however, in line with Endicott *et al*
17 we apply a six point Likert scale to be able to detect subtle changes. We compare changes over time of PMS symptom intensity and interference across three menstrual cycles. The *PMS symptom intensity score* is derived from the first 27 items of the German PMS symptom diary, and the *symptom interference score* is derived from the last three items. With regard to symptom intensity, two additional subscales are calculated by dividing the 27 symptom items into a psychological symptom intensity subscale and a physical symptom intensity subscale score (see secondary outcomes).^17^

Following Kues *et al*
18 and Janda *et al*,^16^ we calculate separate scores for the luteal and follicular phase and consider the difference for our analysis. In more detail, we conservatively consider 7 days prior to menstruation onset as a time slot for the luteal phase and 7 days of the follicular phase, whereas the start of the follicular phase for each participant is calculated using the following formula: (individual cycle duration in days−14)/2=first day of the follicular phase. Subsequently, we calculate the difference score of the means for each menstrual cycle for the respective primary outcome of interest (ie, for PMS symptom intensity or interference). Intensity and interference are considered as marked if rated by participants with at least a 4 (very strong) on a scale from 0 (not at all) to 5 (extreme). Moreover, the item has to be rated with at least a four for at least two consecutive days to be considered as marked. Further, symptoms only are considered as marked symptoms if the respective symptom is not marked in the follicular phase and if it is associated with marked interference in the luteal phase. If a participant has four or more symptoms marked in the luteal phase, also interference of only 1 day is accepted. We are also interested in the trajectory of the symptoms in the intervention groups across the two luteal phases after t0. Hence, we will compare if there are differences of group effects at cycle 2 (C2) and cycle 3 (C3) in contrast to cycle 1 (C1).

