### Statistical analysis

For the testing of the primary hypotheses, the daily data from three menstrual cycles of a symptom diary is examined. Because of the hierarchical structure of the data (menstrual cycles as level-1 are nested within participants as level-2) and given our aim to predict post-interventional changes between menstrual cycles as the primary outcome, a multilevel modelling approach will be adopted. Multilevel models take care of the interdependence of the hierarchical data that arises due to the fact that observations within the same individual are typically more similar to each other compared to observations between individuals.^30 31^ Here, we will analyse temporal changes across menstrual cycles of symptom intensity and interference among the different study groups. To compare a TAU group with two intervention groups and to evaluate the effect of the applied treatment rationale, the following linear a priori contrast will be tested for the factor study group: TAU<OLP−<OLP+. Thus, based on published findings,^6^ we expect that the effect of OLP− lies between that of TAU and OLP+. Out statistical model contains menstrual cycle as within-subject factor with three levels (C1, C2 and C3), study group as between-subject factor with three levels (TAU, OLP+ and OLP–), and the interaction between the two factors. In line with recommendations by Fitzmaurice *et al*,^32^ we will treat baseline values (ie, values at C1) as a part of the outcome vector and assume that the means among study groups are equal at baseline since participants are randomised. The model contains the two main effects study group contrast (defined above) and menstrual cycle (temporal effect) plus the interaction between the two. We will be primarily interested in the interaction term as it tests for the differential temporal change between study groups in order as defined in the linear contrast.

Analyses of secondary outcomes are based on the same multilevel model as used for primary outcomes, but will be considered exploratively, thereby not correcting for multiple tests.^33^

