## Discussion

Given the huge burden of women suffering from PMS,^11 36^ it is necessary to optimise treatment options and to enhance the understanding of intra-interventional processes in PMS treatment. Moreover, interventions - including medical or psychotherapeutic treatment - can generally benefit from an increased comprehension of treatment context-factors and related meaning responses^37 38^ involved in ailment amelioration. We therefore address the investigation of PMS-interventional context-factors and OLP effects and mechanisms with our study and strive to contribute to further knowledge in both areas. Previous randomised controlled trials of PMS interventions indicate high placebo responses.^7^ The presented trial is essential to test whether an OLP response can also be elicited in PMS and whether an amelioration of symptoms occurs primarily on a somatic or psychological level. Additionally, we assess the importance of a comprehensive treatment rationale in a clinical population independent of a specific intervention.

So far, there have been different aspects of previous OLP studies which have been critically evaluated in a meta-analysis of clinical OLP studies.^39^ For instance, a lack of an adequate control group in OLP trials has been pointed out. To address this issue, the TAU control group of our trial has the same amount of contact with the study staff as the two intervention groups. Furthermore, we added an OLP− group to test the effect of a comprehensive OLP treatment rationale in a clinical population. Hence, we aim to assess whether placebo pills alone are sufficient or whether a comprehensive treatment rationale is vital to elicit an OLP response and, thus, strive to distinguish OLP effects from positive framing.^39^

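### The article asks whether the OLP response is primarily physical or psychological, but the stated analysis of two separate subscores contains no test of a difference between the domains

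*Protocol article*

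**What the plan says.** The aim appears in three places, worded in two ways.

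- Secondary outcome measures, on the physical and psychological subscales: "To test whether an OLP response occurs primarily on physical or on psychological symptoms". This is comparative.
- Discussion: the trial is presented as essential for testing "whether an amelioration of symptoms occurs primarily on a somatic or psychological level". This is also comparative.
- Secondary objectives: "To test whether an OLP response is observed for somatic or on psychological symptoms". This asks about the presence of a response, not about which domain responds more.

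The Primary outcome measures section derives the scores by "dividing the 27 symptom items into a psychological symptom intensity subscale and a physical symptom intensity subscale score". The secondary outcome section then assigns 14 items to the psychological score and, by its own count, seven to the physical score; eight physical items are listed.

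On analysis, the Statistical analysis section says: "Analyses of secondary outcomes are based on the same multilevel model as used for primary outcomes, but will be considered exploratively". It describes the model as follows: "The model contains the two main effects study group contrast (defined above) and menstrual cycle (temporal effect) plus the interaction between the two". The group factor enters through a linear ordering of TAU, OLP− and OLP+.

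**The concern.** Whether a response is *primarily* in one domain depends on the effect in that domain minus the effect in the other. Two separate group-by-cycle models give two effects, each tested against zero. Neither gives the difference, its standard error or its interval. Because the two scores come from the same women, that standard error cannot be recovered from the two separate outputs without the correlation between them.

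The easy route to an answer is then to see which subscore reaches significance. That comparison does not test a difference: one effect can fall just above the threshold and the other just below it when both are the same size. At stake is a statement about where open-label placebo works, on a question that the Discussion treats as a main reason for the trial.

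**Working it through.** **1. The plan's own figures.** The Sample size section gives no figure for a comparison between domains. Its stated sample sizes reproduce with the noncentral F distribution (f = 0.25, alpha 0.05): 158 and 206 for the ANCOVA at power 0.8 and 0.9; and 36, 30 and 108 for the repeated-measures interaction, cycle effect and group effect (three groups, three cycles, correlation 0.5, power 0.8).

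**2. Does any stated term answer the question?** The model terms are group contrast, cycle, and group contrast by cycle. The comparative question needs group contrast by cycle by domain. No section names a domain factor, a joint model of the subscores or a difference score.

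**3. Power per domain under the plan's d = 0.5.** Take one change score per domain with SD 1, 50 women per group, and OLP− midway between the other groups. The contrast between the extreme groups has SE = √(2/50) = 0.20. The noncentrality is 0.5/0.20 = 2.5, and power is Φ(2.5 − 1.96) ≈ 0.705. This simplifies the three-cycle model.

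**4. Probability that exactly one domain is significant when the true effects are equal.** Let each two-sided 0.05 test have power p, with correlation r between the two test statistics (bivariate normal, mean 1.96 + z_p). Then

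P(exactly one) = 2(1 − p) − 2·P(neither).

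Example with p = 0.80 and r = 0.5: P(neither) = 0.0871, so 0.40 − 0.174 = 0.226.

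| Power per domain | r = 0.3 | r = 0.5 | r = 0.7 |
|---|---|---|---|
| 70% | 34% | 29% | 22% |
| 80% | 27% | 23% | 17% |
| 90% | 16% | 14% | 11% |
| 99% | 1.9% | 1.7% | 1.5% |

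These figures count both directions. With equal power, either named direction has half the probability. Simulating 20,000 trials of 3 × 50 women under step 3 gave 35%, 29% and 22%, in line with the first row.

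**5. The direct test.** Test the same contrast on the within-woman difference of the two scores, whose SD is √(2(1 − r)). With equal true effects, the simulated false-positive rate was 4.8%, 4.8% and 5.0% at r = 0.3, 0.5 and 0.7. With d = 0.5 in one domain and 0 in the other, the noncentrality is 2.5/√(2(1 − r)) = 2.11, 2.50 and 3.23. The simulated power was 55%, 70% and 89%.

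**6. Item counts.** Breast tenderness, breast sensitivity, breast swelling, headache, joint pains, muscle pain, general body swelling and weight gain make eight items, not seven. Also, 14 + 8 = 22 (or 14 + 7 = 21), although 27 items are said to be divided between the two scores.

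**The case against.** Several points on the other side stand.

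- *The formal objective is not comparative.* The Secondary objectives ask whether a response is observed, and the strengths list mentions only responses on a somatic and a psychological outcome. Two separate models can answer that. The mismatch is confined to the outcome section and the Discussion.
- *No faulty decision rule is written down.* A reader might infer that the trial will call one domain primary because its p-value is below 0.05 and the other's is not. No section says so, and separate models also yield estimates that can be set side by side. The percentages above describe a risk if significance is compared, not a procedure the plan prescribes.
- *The analysis is exploratory and the article is condensed.* Detail may sit in an analysis plan that is not shown. This limits the weight of the point but does not remove it, because the article does name the model for secondary outcomes and that model does not address the comparative wording.
- *The size depends on power.* Under the plan's own interaction assumptions, 150 women give a noncentrality of 0.0625 × 150 × 3/0.5 = 56.25 and power above 0.999, where discordance is close to zero. It matters when the true effects are more modest.

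A reader might also infer that the longer psychological scale will win simply because it is more reliable. The documents do not support this. It needs an assumed inter-item correlation, equal in both domains. Even at 0.3, reliabilities of 0.857 (14 items) and 0.774 (8 items) reduce a latent d of 0.5 to 0.46 and 0.44, a small gap. Standardising to the observed C1 SD would not remove that gap, so it is at most a caveat.

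**Conclusion.** The point holds in limited form. Two sections of the article ask a comparative question that the stated model cannot answer, while the Secondary objectives word the same aim in a way the model can answer. If the separate results were compared by significance, a spurious domain difference would appear in roughly one trial in three to one in nine for power of 70–90% per domain, and in about 2% at 99%. A direct test would hold this at about 5%. The ranges rest on assumed per-domain power, between-test correlations of 0.3 to 0.7, equal true standardised effects and one change score per domain. The analysis is secondary and exploratory, so the primary outcomes, sample size and data collection are untouched.

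**What to change.** Choose one of two routes.

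1. **Keep the comparative question.** Add one exploratory model containing both subscores on a common scale (mean per item, or units of the C1 SD), with symptom domain as a within-woman factor. Report the group-contrast-by-cycle-by-domain term with its confidence interval, and describe a response as primarily physical or primarily psychological only on that basis. Keep the separate subscore results as description.
2. **Drop the comparative question.** Align the outcome section and the Discussion with the wording of the Secondary objectives and make no statement about which domain responds more.

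Under either route, first reconcile the physical subscore (seven stated, eight listed) and state which of the 27 items belong to neither score.

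The first route costs one further model on diary data already collected. Its drawback is precision: the SE of the domain contrast is √(2(1 − r)) times that of a single subscore, which is 1.18 at r = 0.3, 1.00 at 0.5 and 0.77 at 0.7. With a low correlation, or with effects in both domains that differ only modestly, the result may well be inconclusive and should be reported as such. The second route costs only a change of wording.

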#### PMS-Impact Questionnaire^19^

The PMS-Impact Questionnaire (PMS-I) measures the impact of PMS with 18 items and provides a total score and two subscales - a psychological impact and a functional impact scale. It was found to be a valid, reliable (Cronbach’s alpha=0.90) and economic assessment tool of PMS impact.^16^ The questionnaire differentiates between functional and psychological impact.^19^ In comparison to the German PMS symptom diary, it covers more domains of daily life (eg, sexual experiences, physical exertion, stress coping) and is more specific for the detection of small changes of PMS impact. The PMS-I is assessed three times during the luteal phase, once during the prospective screening (L1) and twice during the intervention phase (L2 & L3).

#### Short Form-12 Health Survey for health-related quality of life^20^

The Short Form-12 Health Survey (SF-12) measures health-related quality of life independent of disorders, comprising 12 items, providing a physical and mental component summary scale. Health-related quality of life is assessed since PMS symptoms have a high impact on women’s quality of life.^21^ Physical health is composed of the dimensions of physical functioning, physical role-functioning, bodily pain, general health; mental health is composed of the dimensions of vitality, social functioning, emotional role-functioning and mental health. The SF-12 is a validated and economic version of the SF36. For our purposes, we ask for ratings of the last week including today (premenstrual phase). The SF-12 is completed three times by participants: during the luteal phase of the prospective screening (L1) and twice during the intervention phase (L2 & L3).

#### Hospital Anxiety and Depression Scale–German Version^22^

The Hospital Anxiety and Depression Scale–German Version (HADS-D) aims to assess anxiety and depression in individuals with somatic conditions and can be used for self-reported severity evaluation. It comprises two subscales (anxiety and depression) with seven items each and with a four-level answer format. The sum score indicates general psychological interference. We decided to use the HADS-D since it is a very sensitive tool for less severe cases of psychological disorders, which is usually the case for patients in a primarily somatic setting. We assess the HADS-D only at L1 during the first luteal phase before the start of the intervention.

#### A scale for assessment of satisfaction in close relationships^23^

The scale for assessment of satisfaction in close relationships (ZIP) is the German version of the relationship assessment scale by Hendrick *et al*
24 and measures satisfaction in romantic relationships. The questionnaire entails seven items and had been shown to have high reliability and a clear unifactorial structure.^24^ The ZIP is rated three times by participants during the luteal phases of the prospective screening (L1) and twice during the intervention phase (L2 & L3).

#### Treatment adherence is measured by counting the remaining pills

Participants are asked to return the blister and pill boxes after the intervention.

Expectancy of relief and desire for relief of premenstrual symptom severity are assessed at t0 by means of a Likert scale ranging from 1 to 6, like the primary outcome measure (German PMS Symptom Diary) and 3 weeks after intervention start.

#### Complementary and Alternative Medicine Beliefs Inventory^25^

The Complementary and Alternative Medicine Beliefs Inventory serves to assess three different aspects of complementary medicine intervention beliefs with a 17-item questionnaire with satisfactory validity and reliability measures. Three dimensions comprise beliefs in natural treatments, participation in treatment and holistic health. Participants fill out the inventory post-treatment at t2.

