**Figure 2 F2:**
[figure not shown]
Overview of study groups. OLP, open-label placebo; TAU, treatment as usual.

The TAU group serves as a control group and has the same amount of contacts with the study team. However, participants of this group do not receive any intervention nor any information concerning the intervention. However, they are told why the control group is valuable and essential for the trial and that they will receive the intervention after study conclusion if desired. They are allowed to continue any medication intake, if the substance does not lead to study exclusion and PMS complaints are still prevalent. The same is warrant for both intervention groups.The OLP+ group obtains the intervention with a plausible treatment rationale. The intervention is provided at the personal meeting at the study site (t0), followed by a second study contact after 3 weeks by phone or if desired by participants again at the study site (t1) and a last post-treatment phone contact and assessment after the second treatment cycle (t2). The intervention consists of an administration of OLP pills including the instruction to take two pills a day for 6 weeks. The pill intake in both OLP intervention groups starts at the very day after the study visit (t0). The study visit (t0) occurs during the first 14 days of the menstrual cycle of each participant, that is, in the follicular phase. Due to the cyclicity of PMS symptoms, we decided to provide the intervention for a longer period of time in contrast to previous OLP studies^1–3^ to encompass at least one whole menstrual cycle. After the explicit mentioning of the pharmacological inertness of the pills in both groups, the OLP+ group receives—in contrast to the OLP− group—additionally a comprehensive OLP treatment rationale (see online supplementary material 3) at t0 as well as at t1. The discussion points encompass: (a) that placebos can be powerful, also for PMS, (b) an explanation on why placebos work, (c) that faithful pill intake is crucial and that doubts do not have a negative effect on the treatment, (d) that placebos have also been shown to work without deception. Moreover, a video sequence of about 2 min is shown of an American NBC news report with German subtitle about an OLP intervention on irritable bowel syndrome including a patient report (see https://www.youtube.com/watch?v=uv0SuWKZjsI&t=1s). Neither participants nor study team members are blinded. Yet besides the treatment provider, study team members are not informed about group allocation to minimise investigator bias. As investigational product, pink oral placebo pills—‘P-Dragees rosa Lichtenstein’ of the German brand *Winthrop—*are administered which are certified placebo pills without any active ingredient and with validated quality. Each pill contains the following substances: lactose monohydrate; magnesium stearate (Ph. Eur.); microcrystalline cellulose; highly dispersed silicon dioxide; white clay, magrogol glycerolhydroxy stearate (Ph. Eur.); Arabic gum; montanglycol wax; povidone (K 25); talcum; titanium dioxide (E 171); erythrosine; aluminium salt (E 127); calcium carbonate; sucrose; glucose syrup; maize starch; macrogol 6000. Also, participants of both intervention groups receive a certificate, confirming that the study medication only contains placebo pills.The OLP− group obtains the same intervention and intake instruction like the OLP+ group and the proceeding is identically. However, no treatment rationale or further treatment explanation is provided.

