#### Item about placebo appraisal of the Questionnaire on Responders’ Attitude Regarding Non-Specific Therapies^26^

At t2, participants rate the item about placebo appraisal online which encompasses the following three questions:

How would you define the term placebo?A rating of the positivity or negativity of the term.Do you believe that physical complaints can get better if you merely belief in the efficiency of a therapy?

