#### Patient–provider connection items of the Healing Encounters and Attitudes Lists–German Short Version^27^

The Healing Encounters and Attitudes Lists - German Short Version (HEAL-S) provides an item bank to measure nonspecific factors in treatment. We collect the patient–provider connection item at t2 to control for the influence of provider perception.

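### Complementary-medicine beliefs, placebo appraisal and provider connection are first measured at t2, so the exploratory analyses cannot tell a prior attitude from a consequence of treatment

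*Protocol article*

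**What the plan says.** **Timing.** Each instrument has its own paragraph under Secondary outcome measures.
- Complementary and Alternative Medicine Beliefs Inventory: "Participants fill out the inventory post-treatment at t2".
- Placebo appraisal: "At t2, participants rate the item about placebo appraisal online".
- Provider connection (HEAL-S): "We collect the patient–provider connection item at t2 to control for the influence of provider perception".

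No earlier measurement of any of the three is stated. Trial treatment and study arms puts t2 after the second treatment cycle. Table 1 puts it on days 1-14 of the fourth menstrual cycle, so after C3, the last outcome cycle.

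**Intended use.** The Secondary objectives include:
- "To assess whether positive attitudes towards complementary medicine are associated with OLP responses";
- "To assess the impact of attitudes towards placebos on the OLP response";
- "To evaluate whether the appraisal of the treatment provider has any effect in regard of the OLP effect".

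**Status.** Statistical analysis names study group contrast, menstrual cycle and their interaction as the model terms. Secondary outcomes use the same model and are exploratory, without multiplicity correction.

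**The concern.** Two of the three objectives are directional: they ask what placebo attitudes and provider appraisal do to the response. The third asks only for an association, but its natural reading is that women with certain beliefs respond better. A score first taken after the response cannot show that the attitude came first. A woman who improved may well think better of placebos, of complementary care and of her provider.

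The placebo item has a second problem. Before it is first asked, OLP+ women have heard the rationale at t0 and again at t1 and have seen a supportive news video. The intervention in one arm works on the very attitude being measured.

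The HEAL-S paragraph also speaks of control. If that means entering the t2 provider score as a covariate, the analysis conditions on something that arm and response can both change.

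At stake is what the trial can say about mechanism, which the Discussion gives as a reason for collecting these questionnaires. A later analysis plan cannot supply a baseline that was never measured.

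**Working it through.** **1. Order of events**

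| Measure | When taken | Relative to treatment |
|---|---|---|
| HADS-D (anxiety, depression) | L1 | before randomisation |
| Expectancy and desire for relief | t0, and 3 weeks after start | at the start and during |
| OLP+ rationale | t0 and t1 | is the treatment |
| C2 and C3 diary | cycles 2 and 3 | outcome |
| Complementary-medicine beliefs, placebo appraisal, provider connection | t2 only | after treatment and C3 |

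The objective on anxiety and depression is matched by a pre-treatment measure. The three objectives at issue are not. A score taken once has no course over cycles, so in the stated multilevel model it could stand only on the predictor side.

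**2. How large the artefact could be (illustration)**

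The plan states no figure for this point. Taken from Sample size: 50 women per group, alpha 0.05 and d = 0.5, here applied to TAU versus OLP+ with OLP− midway. Everything else is assumed: prior attitude has no effect on response; b is the shift in t2 score per SD of response; a is the TAU-to-OLP+ shift in t2 score caused by the arm itself, in SD.

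*Correlation within one arm.* If the t2 score is an unrelated prior score (SD 1) plus b times response (SD 1), then r = b/√(1+b²).
- b = 0.3: 0.3/√1.09 = 0.29
- b = 0.5: 0.5/√1.25 = 0.45
- Smallest significant |r| at n = 50 (48 df, t = 2.01): 2.01/√(2.01² + 48) = 0.28

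*All 150 women.* Response was regressed on the linear group contrast and the score in 4,000 simulated trials per setting, with the t2 score scaled to a within-arm SD of 1. The expected adjusted effect under this set-up is d_adj = d(1 − b²) − ab. For example, with a = 0.5 and b = 0.4 it is 0.5 × 0.84 − 0.20 = 0.22.

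| a | b | Significant, baseline score | Significant, t2 score | d_adj, formula | d_adj, simulated |
|---|---|---|---|---|---|
| 0 | 0 | 4.3% | 4.3% | 0.50 | 0.50 |
| 0 | 0.2 | 5.6% | 68.0% | 0.48 | 0.48 |
| 0 | 0.4 | 4.6% | 99.9% | 0.42 | 0.42 |
| 0.5 | 0 | 4.8% | 4.8% | 0.50 | 0.50 |
| 0.5 | 0.2 | 5.2% | 69.2% | 0.38 | 0.38 |
| 0.5 | 0.4 | 4.5% | 99.9% | 0.22 | 0.22 |

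Feedback from response to score (b above 0) creates the false association. It also attenuates the adjusted effect, more so when the arm shifts the score too. In this set-up a shift by arm alone (b = 0) does neither.

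**The case against.** Much of the case on the other side stands.

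- **The primary analysis.** A reader might infer that the primary OLP+ effect is biased. The stated model contains none of these scores. The phrase about control in the HEAL-S paragraph has no model attached, and could mean only a check that provider perception is similar across arms. Bias to a treatment effect is conditional on the score being used as a covariate.
- **Baseline traits and moderators.** A reader might infer that the plan treats these scores as baseline traits or promises a moderator analysis. It does neither. It uses the word baseline only for anxiety and depression, and the complementary-medicine objective asks only for an association, which a t2 score can describe.
- **Moderation is not shown.** Equal feedback in every arm produces a correlation without an attitude-by-arm interaction. The figures above concern association, not spurious moderation.
- **Provider connection.** It cannot be rated before the provider is met at t0, so it has no baseline version.
- **The placebo item.** Asking women before allocation what a placebo is, and whether belief can relieve complaints, could prime all arms on what the trial manipulates. Late placement is defensible.
- **The inventory.** It covers natural remedies, taking part in one's own care and a holistic view of health. The rationale and video are about placebos, so contamination by them is less evident here; feedback from response remains.

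The question of order is not answered by this. Exploratory status lowers the stakes but does not tell cause from effect, and two objectives remain directional in wording.

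**Conclusion.** The point holds in limited form. All three instruments are taken only at t2, and the analyses built on them cannot separate prior attitude from a result of treatment. Adjusting a treatment effect for the t2 provider score could bias it. The primary test is not affected as written.

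The documents give no basis for a size. Under the assumed feedback of 0.2 to 0.4 SD, false associations would be common (68% to over 99%). Adjustment would take a true d of 0.50 to between 0.48 and 0.22, depending on whether the arm also shifts the score. These are illustrations, not estimates for this trial.

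The timing rests on the text of the outcome sections, since Table 1 as available shows no separate rows for these instruments. This is an inexpensive improvement to exploratory objectives, not a threat to the trial's main conclusion.

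**What to change.** 1. For women who have not reached L1, collect the complementary-medicine inventory at that online assessment. It precedes randomisation and already carries the HADS-D.
2. Label t2 inventory scores from women already past L1 as post-treatment, and do not pool them with L1 scores as if they were baseline.
3. Keep the placebo item at t2. Report it and the provider-connection score by arm as post-treatment outcomes, or as post-treatment associations with response, with no predictor or moderator claim. Reword the two directional objectives to match.
4. State what control means in the HEAL-S paragraph, and do not use the t2 provider score as a covariate in efficacy models.

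**Cost.** Items 2 to 4 are wording. Item 1 is a small survey amendment and a few more minutes at L1. Priming should be slight, because the inventory's stated dimensions do not include placebo and recruitment already advertises an integrative treatment. The real cost is a sample split between pre- and post-treatment measurement: enrolment began in August 2018 with completion expected by spring 2020, and the number of women still to reach L1 is not given. If few remain, relabelling is the whole remedy.
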